### Methods for additional analyses (e.g., subgroup analyses) {20b}

We plan to analyse the primary outcome separately in patients who require mechanical ventilation at baseline from those who do not and we in patients above or below 70 years of age as a priori subgroup analyses.

### Methods in analysis to handle protocol non-adherence and any statistical methods to handle missing data {20c}

Primary and secondary outcomes will be calculated and reported for all patients that were found to have COVID-19 infection at enrolment and received at least one dose of study medication or placebo, whilst those who were randomised based on clinical suspicion and later found not to have COVID-19 will be excluded (per-protocol analysis). Adverse events and safety outcomes will be reported as intention-to-treat analysis. No replacement of study subjects or imputation of missing data will be made.

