#### Exclusion criteria

Symptoms of febrile disease for ≥ 1 week at enrolmentPregnancy or inability/unwillingness to perform pregnancy test at and 28 days after enrolmentTreatment limitations in place or moribund patientsAllergy, intolerance or contraindication to any study drug, such as long QT syndromes, myasthenia gravis, pre-existing maculopathy or retinopathy, allergies or known deficiency of glucose-6-phosphate dehydrogenaseKnown HIV positivitySignificant liver disease such as cirrhosis Child-Pugh C or active hepatitis B or CKnown stage IV chronic kidney disease, on dialysis at enrolment or imminent need of itParticipation in another outcome-based interventional trial within the last 30 daysPatients taking hydroxychloroquine for other indication than to treat COVID-19

Comments to the inclusion criteria: For the purpose of this study, intensive care unit is defined as a facility that allows continuous monitoring of vital functions and oxygen administration. In other cultural contexts, this could include also high dependency unit and intermediary care units or level 2 units.

It is expected that most patients will have rtPCR test known within 24 h of admission to hospital. Nonetheless, if this is not the case (e.g., due to overloaded lab facility, lack of supplies) it is possible to randomise a patient based on a strong clinical suspicion of SARS-Cov-2 infection. In the case COVID-19 is not confirmed in retrospect, experimental therapy is withdrawn, and the study subject is withdrawn from “per protocol” analysis of the primary and secondary outcomes but remains in an “intention-to-treat” cohort for the analysis of safety.

Eligibility criteria for study sites. Study sites were selected based on track-record of performing multi-centre interventional studies and willingness to participate.

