### Criteria for discontinuing or modifying allocated interventions {11b}

In general, the study subject will be withdrawn from the study if any of the following criteria are fulfilled:
Consent withdrawal by study subjectIn case—in the opinion of the investigator—the study procedures are considered unsafe for the study subject or the risks outweigh the potential benefits

Specifically, for the study subjects enrolled into the study as COVID-19 suspected but without the definite result of rt-PCR testing:
If COVID-19 is negative and believed to be true negative, subjects will be immediately withdrawn from the study and administration study medication will immediately be stopped. Yet, data on adverse events will still be collected and analysed, in accordance with “intention-to-treat” mode of safety analysis

Note: In case there is a strong suspicion of COVID-19 despite negative test or if there is a doubt about the validity of the test (e.g., questionable sampling technique), it is possible and recommended to repeat the test and only withdraw the subject from the study after the confirmatory test is negative.

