### Sample size {14}

Based on data from Wuhan [6] and Washington [7], where 67% of patients had died within 2 weeks and half of the survivors needed protracted mechanical ventilation, we assume the incidence of the primary outcome in the control group (i.e., being alive and off the ventilator in 2 weeks) to be 25%. The study gives us 80% chance to detect the increase of the primary outcome to 50% in one or both interventional groups at *p* < 0.017 with 74 patients in each arm. In order to compensate for drop-out and loss of follow up, we plan to enrol 240 subjects into the study. No replacement of subjects who dropped out from the study is planned.

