## Statistical methods

### Statistical methods for primary and secondary outcomes {20a}

The proportion of patients alive and off mechanical ventilation (primary outcome) between intervention and control groups will be calculated using chi-square test. *p* value is adjusted for multiple comparisons to *p* = 0.017 as there are 3 comparisons between 3 study arms. Survival and ICU/length of stay will be compared using Kaplan-Maier’s curves and exploratory analyses my multi-level regression using statistical packages in software in R. We plan to analyse the primary outcome separately in patients who require mechanical ventilation at baseline from those who do not and we in patients above or below 70 years of age as a priori subgroup analyses.

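### Efficacy is calculated only in confirmed, dosed patients, with no all-randomised efficacy analysis and no stated outcome follow-up after withdrawal, so the randomised comparison is not protected

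*Protocol article*

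**What the plan says.** The section on non-adherence and missing data {20c} fixes the efficacy set. Patients count if they were found to have COVID-19 at enrolment and took at least one dose of drug or placebo, whereas "those who were randomised based on clinical suspicion and later found not to have COVID-19 will be excluded (per-protocol analysis". The comments under the exclusion criteria {10} agree: a patient whose infection is not confirmed in retrospect "is withdrawn from “per protocol” analysis of the primary and secondary outcomes". The interim analysis section {21b} repeats the confirmed-and-dosed restriction and then gives the efficacy stopping criterion at p < 0.017, so the interim look uses the same set. Intention to treat is mentioned only for adverse events and safety. On missing data, {20c} says: "No replacement of study subjects or imputation of missing data will be made".

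The section on discontinuing or modifying interventions {11b} governs who leaves. Someone enrolled on suspicion is withdrawn when a negative result is thought to be genuine. If doubt remains the test may be repeated, and sites should "only withdraw the subject from the study after the confirmatory test is negative". Adverse events are still collected in these patients; day-14 status is not mentioned. The same section also withdraws a patient from the study when, in the investigator's opinion, "the study procedures are considered unsafe for the study subject or the risks outweigh the potential benefits".

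The section on adherence {11c} lets doses be omitted in patients who cannot take anything enterally and gives profound shock as an example.

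**The concern.** Randomisation makes the arms comparable for everyone randomised. A subset chosen by later events keeps that comparability only if those events are unaffected by treatment. Here the subset is the only efficacy population described.

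Three routes need attention:

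- **Test result.** No rule requires the deciding sample to be taken before the first dose. The trial's hypothesis is that the drugs suppress viral replication, and a negative day-14 swab is itself an exploratory outcome. A negative result obtained after dosing could therefore be partly a treatment effect.
- **No dose received.** Failure to receive a first dose is tied to severity. An unblinded pharmacist prepares the drug and is also responsible for its timely administration.
- **Withdrawal as unsafe.** Stopping study drug and leaving the study are not separated. The Discussion names QT prolongation and arrhythmia as possible harms, so such withdrawals could be more frequent on active treatment. If day-14 status is then not collected, no later analysis plan can recover it.

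Without an all-randomised result, a reader cannot judge whether any of this changed the answer.

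**Working it through.** **1. Reproduce the planned size.** Inputs from Sample size {14}: control success 25%; "The study gives us 80% chance to detect the increase of the primary outcome to 50% in one or both interventional groups"; 74 per arm; 240 enrolled, so 80 per arm at 1:1:1. From {20a}: chi-square test and p = "0.017 as there are 3 comparisons between 3 study arms". Two-sided testing is assumed.

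Unpooled formula: n = (z₁₋α/₂ + z₀.₈)² × [p₁(1−p₁) + p₂(1−p₂)] / (p₂−p₁)². With α = 0.05/3: (2.394 + 0.842)² × (0.1875 + 0.25) / 0.0625 = 73.28, so 74. The plan's figure reproduces. The pooled form at α = 0.017 gives 77.

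The loss allowance is 240 − 3 × 74 = 18 patients, or 18/240 = 7.5%. It is justified by drop-out and loss to follow-up only, but it must also absorb every exclusion, because nobody is replaced.

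**2. Size of a possible bias (assumed).** Suppose there is no true effect, 25% success in both arms, and all removed patients are failures. If a share w is removed from one active arm, its observed success is 0.25/(1−w).

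For w = 0.10: 0.25/0.90 = 27.8%, with 72 patients against 80.
- Pooled rate = (20 + 20)/152 = 0.263.
- Null standard error = √[0.263 × 0.737 × (1/80 + 1/72)] = 0.0715.
- Critical difference = 2.387 × 0.0715 = 0.171.
- With a shift of 0.028 and an unpooled standard error of 0.0716, the two rejection tails sum to about 0.026.

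| Removed, active arm | Removed, control | Observed success, active / control | Type I error |
|---|---|---|---|
| 0 | 0 | 25% / 25% | 0.017 |
| 5% | 0 | 26.3% / 25% | 0.019 |
| 10% | 0 | 27.8% / 25% | 0.026 |
| 10% | 5% | 27.8% / 26.3% | 0.019 |
| 20% | 0 | 31.3% / 25% | 0.062 |
| 10% | 10% | 27.8% / 27.8% | 0.017 |

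The last row matters: equal removal in both arms leaves the error rate unchanged.

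**3. Power of the two sets (assumed share of true negatives).** The article gives no such share. Pooled chi-square, α = 0.017, 80 randomised per arm. For intention to treat, a share d has no treatment effect and a success rate q of 25–75%, so each arm's rate is (1−d) × p + d × q. At d = 10%, q = 25%, the comparison is 25% against 47.5%, with power 72%. At q = 75% it is 30% against 52.5%, with power 70%.

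| True negatives | Confirmed set: n per arm, power | Intention to treat, 80 per arm | n per arm for 80% power, intention to treat |
|---|---|---|---|
| 0% | 80, 82% | 82% | 77 |
| 5% | 76, 80% | 76–77% | 85–87 |
| 10% | 72, 77% | 70–72% | 94–99 |
| 20% | 64, 71% | 56–61% | 118–128 |

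**The case against.** A fair defence has four parts.

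- **Infection at enrolment is a baseline state.** Section {20c} words it that way, and {10} expects most results within 24 h of hospital admission. A patient already positive is not removed for clearing the virus later. The repeat test exists to keep strongly suspected patients in, and site investigators are blinded {17a}. This stands as a limit on size: the clearance route is narrow. It does not close the route, because no pre-dose sample is required and the final call is a judgement.
- **Withdrawal as unsafe is not an efficacy exclusion.** A reader might infer from {11b} that these patients are dropped from the analysis. The text does not support that: by {20c} a confirmed, dosed patient stays in the set. Loss of the day-14 outcome is an inference from study withdrawal plus no imputation. The article condenses a full protocol, which may set out follow-up. What remains is a risk, not a stated exclusion.
- **No figure shows a difference between arms.** The article gives no expected rate of exclusion or withdrawal, and the example in the working assumes one-sided removal of failures only. That is correct, so the example is an illustration and not an estimate.
- **The remedy costs power.** With 10% true negatives, intention to treat at 80 per arm has 70–72% power against 77% in the confirmed set. This stands, and it makes the choice of primary set partly a trade-off.

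**Conclusion.** The point holds in a limited form. The article states, and does not merely leave open, that efficacy is calculated only in confirmed, dosed patients; it describes no all-randomised efficacy analysis. Two grounds for exclusion arise after randomisation, and the day-14 outcome of withdrawn patients is not secured. The randomised comparison is therefore not protected.

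A reader might go further and conclude that the comparison is broken, that withdrawn patients have no follow-up at all, or that the bias favours the drugs. The document supports none of these. Exclusions that do not differ by arm leave type I error at 0.017, adverse events are still collected in patients found negative, and no direction of bias can be derived from the text.

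The possible size is modest unless losses are large and one-sided: about 0.026 instead of 0.017 at 10%, and 0.062 at 20%, both under the extreme assumption that every removed patient failed. The reason to act is that outcomes not collected during recruitment may not be recoverable later, while collecting them costs little.

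**What to change.** Amend {10}, {11b}, {20c} and {21b}:

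1. Separate stopping study drug from leaving the study. The clinical rules for stopping drug need no change.
2. Collect day-14, day-28 and day-90 outcomes for every randomised patient who has not withdrawn consent, including those found negative.
3. Define confirmed infection only from samples taken before the first dose, adjudicated blind to allocation.
4. Report an all-randomised intention-to-treat efficacy analysis, preferably as primary. At the least, pre-state it beside the confirmed-infection set, and drop the at-least-one-dose condition from that set.

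The cost in effort is an amendment and some further contacts by a route that {13} and {18b} already provide, by telephone where needed. The cost in power should be stated openly. If intention to treat is primary, 80 per arm gives 80% power only if true negatives are rare; at an assumed 5% or 10%, 85–87 or 94–99 per arm would be needed. If the sponsor will not enlarge the trial, keeping the confirmed-infection set as primary is defensible, provided that it rests on pre-dose samples and the all-randomised result is reported with it.

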### Plans to give access to the full protocol, participant level-data and statistical code {31c}

Full protocol is available on the website www.donatio-intensivistam.cz and de-identified participant-level dataset will be made available 6 months after the publication of the results of the study at www.mendeley.com.

## Oversight and monitoring

### Composition of the coordinating centre and trial steering committee {5d}

The steering committee consists of the principle investigator, one investigator representative from each study site, lead study pharmacist, research methodologist, study statistician and patients’ representative. Non-voting members are the central study coordinator and legal advisor. The main role of the steering committee is overall supervision of the trial; the committee meets at least biannually, to review all reported SUSARs as well as new evidence in the field of COVID-19 treatment. The committee makes by majority vote the final decision as to whether to stop or continue the trial after interim analysis or should any safety concerns arise. The principle investigator chairs the steering committee and reports to the sponsor and legal authorities such as REB or SUKL.

### Composition of the data monitoring committee, its role and reporting structure {21a}

The funder appointed an independent data monitor. The eCRF is designed to generate queries and reports on missing data or unusual data entries, which will be fed back to the study site investigators in regular intervals.

### Adverse event reporting and harms {22}

The study will be conducted in accordance with the protocol, Good Clinical Practice and current Czech legislation. It is of upmost importance for the safety of all subject in this and other trials that all personnel involved in this trials complies with the KLH-21, version 7, directive of SUKL on Reporting Adverse Reactions to Medicinal Products for Human Use in a Clinical Trial and to Medicinal Products without Marketing Authorisation, issued in accordance with the provisions of Section 56, point 13 Act No 378/2007 Coll., on Pharmaceuticals and on Amendments to Some Related Acts, as amended. In particular, the investigator is obliged to promptly report all SUSARs to the sponsor. A prompt report (no later than within 24 h from the moment when the investigator has learnt about the fact) will be followed by detailed written reports. In prompt and follow-up reports, subjects are identified using unique numerical codes, which were assigned to the subjects.

Of note, this clinical trial is performed on a population of critically ill patients with a very high mortality rate. Therefore, if the death of a study subject is deemed by the investigator as resulting from the natural course of the underlying disease and no relation to study treatment or procedures is suspected, such an event shall not be considered SAE and reported as such.

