### Who will take informed consent? {26a}

There is a three-step process of obtaining informed consent process compliant with Declaration of Helsinki (ver. 2008): (1) Patients with decision-making capacity will be asked by study physician to provide written prospective informed consent and consent for the use and storage of personal data as per Regulation (EU) 2016/679 General Data Protection Regulation (see Appendix). It is expected that a significant proportion of screened patients will lack the capacity to provide informed consent due to altered consciousness, respiratory distress, or sedation to facilitate mechanical ventilation. In this situation, (2) the deferred consent policy [6] will be applied in patients without capacity: patient’s legal representative will be sought to consent for the patient and if not available or approachable with reasonable effort, (3) the patient will be enrolled without consent. In the latter case, an independent physician will confirm in writing that the patient fulfils criteria and lack capacity. The patients themselves are approached to provide ongoing consent as soon as they regain capacity. They are given options to continue in the study, to withdraw with permission to use the data collected up to the point or to withdraw from the study and request deleting all data collected. This trial is fully compliant with both Declaration of Helsinki (ver. 2008) and Czech legislation. The family will be informed when practical about their relative’s enrolment into the trial based on the opinion of the independent physician and the family will be offered an information leaflet explaining the nature of the study. In the case they are of the opinion that the patient would not wish to participate in the trial, patients will be withdrawn. All serious adverse events that are suspected from being related to study interventions will be reposted to Research Ethics Board and regulatory authorities as per local legislation.

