### Interim analyses {21b}

We plan to perform an interim analysis after the primary outcome is known for the 120th subject. As mentioned above, primary and secondary outcomes will only be calculated in patients with confirmed COVID-19 infection who received at least one dose of IP. Adverse events will be calculated in all randomised patients (intention-to-treat analysis).

All suspected unexpected serious adverse events (SUSARs) will be reported to both REB and to the steering committee, who may decide to stop the trial for safety concerns. Apart from safety, other reasons for stopping the trial are as follows:
Emergence of new data (e.g., publication of the results of a big RCT) that may lead the continuation of the trial unethical. This may be due to safety concerns of the placebo group (in case a strong clinical benefit is proven by other trials) or any of the interventional groups (e.g., if harm is reported by other trials). This rule also applies for emergence of a new treatment.After interim analysis: The steering committee will review primary outcomes and the summary of adverse events in all 3 groups (labelled as A, B, and C) whilst still blinded to treatment allocation. The treatment can be stopped if the following criteria are fulfilled:There is a significant difference in the primary outcome at *p* < 0.017 in between the groups.Futility: The futility criterion is not binding for the steering committee. Based on available data, the study statistician calculates the probability of being able to prove the null hypothesis with achieving the target number of subjects and the probability of type II error made by stopping the trial prematurely.Safety: In case the number of adverse events in one or more treatment groups is found uneven or unacceptably high.Details of pharmacovigilance are described in a dedicated section below.

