## Discussion

This is an investigator-initiated trial endorsed by the Czech Society of Anaesthesia and Intensive Care. The most significant resource for the study is unpaid voluntary work of all the personnel conducting the study, who decided to do so in times of worldwide pandemic crisis. Part of the resources was gathered from voluntary donors in a crowdfunding campaign conducted by the medical student association. The pharmaceutical company Zentiva ltd. was approached by investigators and kindly agreed to provide study medication at no cost; however, it has had nor will have any role in study design; collection, management, analysis, and interpretation of data; writing of the report; or the decision to submit the report for publication.

This trial investigates two drugs that are being used off label to treat patients with severe COVID-19 with a balance of potential benefits and harms. In vitro and observational trial suggest their potential to limit viral replication and the damage to lungs as the most common reason for ICU admission. Therefore, patients most likely to benefit from the treatment are those with severe, but early disease. The potential benefit is based on biological rationale and observational data [5] showing that one or both drugs may prevent progression of a disease which led to death in 67% of patients in a similar condition to those we plan to randomise [11]. Possible harms include QT prolongation and resulting life-threatening arrhythmias or retinopathy, which may result in blindness. We believe that clinical equipoise regarding risk/benefit to the individual patient justifies well the conduct of this RCT.

We acknowledge that the power of this study is relatively low, as it is only powered to detect 25% difference in the primary outcome. This is why we decided to make de-identified participant-level data available in a public database so they can be used in patient-level meta-analyses should trials with a similar or identical design are conducted anywhere in the world.

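### Deaths attributed to COVID-19 lose SAE status and the interim names no all-cause death count, so an excess of deaths between arms may be under-detected

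*Protocol article*

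**What the plan says.** All references are to the protocol article.

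- **Exemption of deaths.** Section {22} notes the very high mortality of this population and takes some deaths out of SAE status: "such an event shall not be considered SAE and reported as such". The exemption applies "if the death of a study subject is deemed by the investigator as resulting from the natural course of the underlying disease". It also requires that the investigator sees no possible link with the trial drugs or trial procedures. Under {17a}, site investigators are blinded to allocation.
- **Interim safety review.** Section {21b} has the steering committee look at the primary outcome and an adverse-event summary in three coded groups. The safety criterion reads: "In case the number of adverse events in one or more treatment groups is found uneven or unacceptably high". Adverse events are counted in all randomised patients. Primary and secondary outcomes are restricted to patients with confirmed infection who took at least one dose.
- **Primary outcome.** It counts a patient as a success only if alive, not in end-of-life care and off mechanical ventilation at day 14. Mortality at days 28 and 90 is a secondary outcome.
- **Reporting outside the interim.** Section {22}: "the investigator is obliged to promptly report all SUSARs to the sponsor". Section {21b}: "All suspected unexpected serious adverse events (SUSARs) will be reported to both REB and to the steering committee". The committee's regular meetings under {5d}, held at least twice a year, are "to review all reported SUSARs as well as new evidence in the field of COVID-19 treatment".
- **A different wording in the consent section {26a}.** "All serious adverse events that are suspected from being related to study interventions" go to the ethics board and the authorities, with no restriction to unexpected events.
- **Named harms.** Discussion: "Possible harms include QT prolongation and resulting life-threatening arrhythmias or retinopathy".

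**The concern.** In a population expected to die often of the disease, a death hastened by a study drug may look like any other COVID-19 death. A blinded investigator judging one case has little to separate the two. A drug effect on mortality shows mainly as a difference between arms, so the committee needs all-cause deaths by arm. The plan sorts deaths by individual attribution first and then bases its safety criterion on adverse-event numbers, without saying whether the sorted-out deaths are still counted.

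There is a second, smaller gap between reviews. The protocol lists life-threatening arrhythmia as a possible harm and refers to the product characteristics for adverse effects. A serious arrhythmia could therefore be classed as expected, would then not be a SUSAR, and need not reach the committee before the interim.

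At stake is whether the people who can stop the trial see the counts they need in order to judge.

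**Working it through.** The plan states no figure for this point, so the main check is a comparison of texts. The arithmetic sizes the gap and shows what the remedy can and cannot do.

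**1. Where an exempted death can appear at the interim**

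| Input to the committee | Population | Does it show an exempted death? |
|---|---|---|
| Adverse-event summary | All randomised | Not stated |
| Primary outcome | Confirmed and dosed, day 14 | Only merged with ventilation and end-of-life care |
| Day-28/90 mortality | Confirmed and dosed | Not among the items named for the committee |

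Three kinds of exempted death are not assured of showing up:
- deaths in randomised patients later found negative or never dosed;
- deaths after day 14;
- deaths by day 14 in patients who would otherwise still be ventilated.

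**2. How the composite can hide deaths (invented counts, 40 per arm)**

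- Arm 1: 20 dead, 10 ventilated, 10 successes.
- Arm 2: 24 dead, 6 ventilated, 10 successes.
- Primary outcome: 10/40 = 25% in both arms.
- Deaths: 20/40 = 50% against 24/40 = 60%.

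**3. How many deaths are involved**

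The interim is at 120 subjects. With 1:1:1 allocation, 120/3 = 40 per arm.
- At the 67% two-week mortality cited under Sample size {14}: 0.67 × 40 = 26.8, about 27 per arm.
- At 50%: 0.50 × 40 = 20 per arm. This is the mortality implied by the planned 25% control rate if half of survivors are ventilated: 1 − 0.25/0.5 = 0.50.
- At an assumed 30%: 0.30 × 40 = 12 per arm.

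Each is a ceiling, reached only if every death is attributed to the disease.

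**4. How attribution shrinks a difference**

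Suppose mortality is 67% in one arm and 77% in another: 26.8 against 0.77 × 40 = 30.8 deaths, an excess of 4.0. If a share q is attributed to the disease in both arms, the deaths left as SAEs are (1 − q) times these:
- q = 0.80: 5.36 against 6.16, an excess of 0.8.
- q = 0.95: 1.34 against 1.54, an excess of 0.2.

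The values of q are assumptions. If exempted deaths still count in the adverse-event summary, this shrinkage does not occur there.

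**5. What a formal test could do at the interim**

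Power for two proportions at two-sided 0.017, normal approximation with pooled variance under the null:

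Φ{ [ |p1 − p2|√n − z√(2p̄(1 − p̄)) ] / √(p1(1 − p1) + p2(1 − p2)) }, with z = 2.387 and p̄ the mean of p1 and p2.

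Check against the plan's own figure: for 25% against 50%, the unpooled sample-size formula gives (2.387 + 0.842)² × (0.1875 + 0.25)/0.0625 ≈ 73 per arm, against the stated 74. The power formula above gives 78.3% at 74, against the stated 80%. The method agrees closely with the plan.

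At 40 per arm:
- Primary outcome falling from 25% to 15%: 10%. To 10%: 26%. To 5%: 55%.
- Mortality rising from 67% to 77%: 8%. To 83.5%: 25%.
- A 20-point rise from an assumed 30% to 50% baseline: 27% to 28%.

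The primary outcome is thus a weak detector of harm at the interim, and a mortality test would be weak too.

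**6. Reporting routes side by side**

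| Section | Events | Recipient |
|---|---|---|
| {26a} | All SAEs suspected to be related | Ethics board and authorities |
| {21b} | SUSARs | Ethics board and steering committee |
| {22} | SUSARs, promptly | Sponsor |
| {5d} | SUSARs and outside evidence | Steering committee, routine meetings |

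For the ethics board, {26a} and {21b} give different scopes. No row sends an expected but serious related event to the steering committee.

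**The case against.** A reader might infer that the safety stopping rule is blind to arrhythmia and death. The text does not support that. The rule runs on adverse events in all randomised patients, not on SUSARs, so a recorded arrhythmia appears in the interim summary whether or not it was expected. Death is a failure in the primary outcome, and a difference at p < 0.017 permits stopping without a stated direction. A death with a suspected link to treatment remains an SAE.

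Nor are SUSARs the only events escalated: {26a} sends all suspected-related SAEs to the ethics board and authorities. Section {22} introduces SUSAR reporting as a particular instance under GCP and a national directive whose content is not shown here. Excess death is also not among the harms the Discussion lists.

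Other safeguards exist. Under {5d} the committee may act on any safety concern and seats an investigator from every site. Under {17b} the principal investigator, who chairs it, must be told of emergency unblinding within 24 h.

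Finally, this is a condensed article, and the contents of interim tables are often left to a fuller document. A separate mortality comparison would have low power.

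Most of this stands, and limits the point to under-detection. Two parts do not answer it. The exemption and the interim inputs are stated affirmatively, and the gap arises from reading them together, not from omitted detail. Low power is no rebuttal either, because the safety criterion is a judgement with no p-value attached, and the committee needs the counts to exercise it.

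**Conclusion.** The point holds as a risk of under-detection and should be corrected. Followed as written, deaths attributed to the disease are assured of reaching the committee only inside a day-14 composite limited to confirmed, dosed patients, where a death in someone who would otherwise still be ventilated changes nothing. The number involved at the interim is at most about 27 per arm at the cited 67% mortality, or about 20 at 50%, assuming equal arms and that every death is attributed to the disease. How many would be exempted in practice cannot be known from the document.

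Between reviews, a serious arrhythmia classed as expected need not reach the committee through the named routes. Whether it would be so classed is an inference from the listed harms, not something the text states.

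The wording of {26a} differs from that of {21b} and {22}, and this needs reconciling in any case. It would go too far to say that the stopping rule cannot see these harms, or that nothing but SUSARs is escalated.

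**What to change.** Keep the exemption of disease-attributed deaths from expedited reporting if wanted. Then:

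1. State in {21b} and {22} that all-cause deaths, and all serious arrhythmias and cardiac arrests, are tabulated by coded group in all randomised patients, whatever the attributed cause or expectedness, at the interim and at each committee review.
2. State whether exempted deaths count in the adverse-event summary.
3. Reconcile {26a}, {21b} and {22} so that each recipient (sponsor, steering committee, ethics board, authorities) has one stated scope of reporting.

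The cost is some wording and one extra table. Vital status is already part of follow-up, and adverse events are already collected in all randomised patients. For patients withdrawn after a negative test, the article keeps only adverse-event data, so it should say that deaths are included. The committee would see coded-group counts more often than at the single interim. The table supports a judgement, and should not be presented as a powered mortality test.
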